## Abstract

**Background:**

On Reunion Island, incidence and mortality for uterine cervical cancer is high, yet coverage rate for human papillomavirus (HPV) vaccination is low.

**Objective:**

The main objective of the study is to evaluate the impact of a health promotion program promoting HPV vaccination on the proportion of middle school girls who complete the full HPV vaccination schedule (2 or 3 doses) by the end of school year.

**Methods:**

This study is a cluster controlled intervention study using a superiority design. A combined health promotion program will be offered containing information to students and parents, training of general practitioners, and free school-based vaccination (in a “health bus”). Children who attend this program will constitute the intervention group and will be compared to children from another middle school who will not attend the program constituting the control group.

**Results:**

Recruitment began in October 2020. In the intervention school, of 780 students, 245 were randomly selected in the 12 classes. In the control school, 259 students out of 834 were randomly selected.

**Conclusions:**

In this study, we explore the impact of a health promotion program combining information toward students, parents, and general practitioners with free school-based vaccination. We expect a significantly higher HPV vaccination coverage in the intervention school as compared to the control school, whether it be among girls or boys. The final implication would be an extension of this program in all middle schools on the Island and thus an increase in HPV vaccination coverage.

**Trial Registration:**

ClinicalTrials.gov NCT04459221; https://clinicaltrials.gov/ct2/show/NCT04459221

**International Registered Report Identifier (IRRID):**

DERR1-10.2196/35695

## Introduction

### Background

On Reunion Island, a French territory located near the eastern coast of Madagascar in the Indian Ocean, uterine cervical cancer is the fourth most common cause of cancer in women, similar to worldwide [1]. However, the standardized incidence rate in 2016 was 8.8 in 100,000 women, 2 times higher than in metropolitan France. The standardized mortality rate follows a similar trend: on Reunion, it accounts for 4.8 in 100,000 women, whereas the metropolitan rate was 1.7 in 100,000 women [2,3].

Cervical cancer results from human papillomavirus (HPV) infection, which is the most common viral sexually transmitted infection. There are more than 100 types of HPV, some of which are high-risk oncogenes, such as HPV 16 and HPV 18, which are responsible for 70% to 80% of invasive cervical cancers [4]. On Reunion Island, most frequent HPV genotypes are HPV 16, HPV 52, HPV 33, and HPV 31, all contained in the nonavalent HPV vaccine [5].

Indeed, prevention of cervical cancer is mainly based on screening by cervical HPV test and on HPV vaccination, which has proven to be effective in reducing the prevalence of HPV transmission but also in reducing the incidence of condyloma and intermediate grade dysplasia [6,7]. Since HPV is mainly transmitted sexually, it is important to vaccinate before the beginning of sexual life.

Because HPV infections can also lead to vulvar, vaginal, penile, anal, or throat cancers, some countries (eg, United States, Canada, Australia, Germany, Austria, Belgium, Italy) recommend gender-neutral vaccination in order to promote herd immunity and reduce circulation of the virus in the general population [6,8]. In France, since December 2019, it is recommended that HPV vaccination should be offered to all children, regardless of their gender, aged 11 to 14 years (2 doses), with catch-up vaccination possible for adolescents aged 15 to 19 years not yet vaccinated (3 doses). Before December 2019, vaccination was only recommended for girls. High levels of vaccination coverage are obtained in countries that vaccinate in schools [9-11].

On Reunion Island, the HPV vaccination coverage rate is the lowest in France, estimated at 8.1% among girls aged 16 years in 2018, while the national average is already low (23.7%) [12].

This low coverage rate on Reunion Island may have several explanations. First, inhabitants seem to be poorly informed about the existence of this vaccine [13]. Moreover, vaccination coverage rates depend on the socioeconomic level of the population. In France, lower rates of HPV vaccination uptake were observed in adolescents with universal health insurance coverage (French equivalent of the US Medicaid program) compared with those not receiving such insurance [14]. Reunion Island is one of the French departments with the highest rates of inhabitants covered by this universal health insurance. Finally, not only is there vaccination hesitancy in general but also most specifically against HPV vaccine, among patients and also among physicians [13]. A total of 41% of Reunion inhabitants hold unfavorable opinions about vaccinations, with the HPV vaccine being among the most frequently cited. Among patients not vaccinated against HPV, 37% stated that the vaccine had not been suggested to them by their doctor, and 7.3% were confronted with doubts expressed by their doctor concerning vaccination in general [13]. However, a systematic review of 79 studies in 15 countries showed that the most important factor influencing HPV vaccination was physician recommendation [15,16]. Indeed, 89.3% of the Reunion population fully trusts their doctor [13]. Therefore, interventions targeting health professionals and especially general practitioners appear to be paramount, especially when combined with interventions targeting the population to be vaccinated [17].

Thus, given the epidemiological situation on Reunion Island (high incidence and mortality for cervical cancer, very low coverage rate for HPV vaccination), we aimed to study the impact of a prevention program against sexually transmitted infections, including pathologies related to HPV, with a program promoting HPV vaccination among young students in middle school.

### Objectives

Hypotheses were as follows: (1) clear and appropriate information for the target population of the vaccination (middle school students aged 9 to 17 years) as well as for their parents will improve their knowledge about HPV vaccination and thus increase their adherence to this vaccination regimen, (2) combining information with vaccination in the school setting will improve coverage, as it will reduce any material obstacles that may prevent the vaccination process, and (3) raising awareness among general practitioners will enable them to better understand the benefits and risks of HPV vaccination and thus encourage families, who naturally trust them, to adhere to the program.

The main objective of the study is to evaluate, in a population of middle school girls on Reunion Island, the impact of a health promotion program on the proportion of middle school girls who complete the full HPV vaccination schedule (2 or 3 doses) by the end of school year.

The program, conducted during school year, will combine: (1) sexual health promotion (students and parents) during classes at school at the beginning of school year, (2) training of general practitioners (who practice in a perimeter of 5 km around the middle school) on HPV vaccination at the beginning of school year, and (3) free school-based vaccination (in a “health bus”) during the academic year.

Secondary objectives in the study population at the end of school year are as follows:

Assess the impact of the combined health promotion program on the proportion of middle school girls who initiated HPV vaccination (at least 1 dose)Assess the acceptability of the HPV vaccination program among middle school boysDescribe the barriers to HPV vaccination for both girls and boysAssess the acceptability of HPV vaccination in the school settingAssess the value of setting up a sexual health information point through a health busEvaluate the satisfaction of students, parents, and school workers with the measures put into placeEvaluate vaccination coverage for different mandatory vaccines according to the current national vaccination calendar

The aim of this study was to evaluate whether a health promotion program combining information and free school-based vaccination could raise HPV vaccination coverage.

## Methods

### Trial Design

This study is a cluster controlled intervention study using a superiority design. Children who will attend the combined health promotion program will constitute the intervention group and will be compared with children who will not attend the program (as is currently the case in all French middle schools), who will constitute the control group.

### Study Setting

This trial will concern Reunion Island in order to investigate the particular epidemiological situation of HPV on the island, even if the results of this study are expected to be applicable to other French regions.

The 2 arms of the trial will be designed to have the most comparable populations and to avoid any risk of contamination between the 2 arms or having general practitioners taking care of children in both schools.

We have thus chosen to carry out a cluster trial. The 2 groups (intervention group and control group) will be selected from a middle schools located in each of 2 cities. In each of the schools, we will randomly draw 3 classes in each grade level (6th, 7th, 8th, and 9th grade) to have a balanced number of students in each arm (see sample size). Thus, 12 classes will be selected for each school.

Provided that there is a relationship between socioeconomic status and vaccination coverage, it was decided to focus the study only on middle schools in priority education zones, which theoretically enroll a population in which HPV vaccination coverage is the lowest. On Reunion Island, 21 middle schools are classified as priority education zones, spread over 7 cities. In agreement with the head of the academy and the school directors, 2 schools have been designated among the abovementioned middle schools: the intervention school will be Paul Hermann Middle School, located in St Pierre, and the control school will be Plateau Goyave Middle School, located in St Louis.

These choices are based on the schools’ ability to participate in this research, their geographical location, and the ability to park the health bus at or in the immediate surroundings of the school of the intervention group. The health bus will be provided by the Association d’Education Thérapeutique et d’Intervention Sociale (ASETIS, or Association for Therapeutic Education and Social Intervention), existing since 1996 and recognized as being of public interest.

### Eligibility Criteria

Inclusion criteria are as follows: enrolled in one of the classes randomly selected in the 2 middle schools designated, affiliated with or benefiting from a social security system, who will agree to participate in the study and whose parents or holders of parental authority will sign a free, informed, and written consent. Exclusion criteria (intervention group only) are as follows: hypersensitivity to the active substances or to one of the excipients of the vaccine (Gardasil 9), a permanent contraindication to vaccination, pregnant or breastfeeding (based on self-reporting), already initiated HPV vaccination (complete or incomplete schedule), or eligible to participate for collection of data but not for vaccination in the health bus; students with an incomplete vaccination schedule will be referred to their general practitioner to complete the missing doses. Vaccinations will be performed by a junior doctor under the supervision of a senior doctor.

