### Intervention Description

#### Intervention Group

Meetings with parents in the intervention middle school will be scheduled at the beginning of school year to inform parents about HPV vaccination and explain this study to them. Consent forms will be collected during these meetings. If assemblies are forbidden by the government because of COVID-19, information meetings for parents will be cancelled. Instead, 6 interventions will be planned.

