##### August-September: Program Information Sent Home to Parents via Students

Written information adapted to student age about HPV vaccination, and documents outlining objectives, interventions, constraints, foreseeable risks and expected benefits of the research, and the rights of the participants in this research context will be sent with children to give to their parents. Consent form to participate to the study to be signed by both parents or holders of parental authority and a sociodemographical questionnaire with questions about HPV knowledge will also be included.

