##### October-November: Contact With Parents and Return of Information to School

Investigation team will call each authority holder individually by telephone to inform them about HPV vaccination, the study, its objective, nature of the constraints, and foreseeable risks and expected benefits of the research. The team will also remind them of the rights of participants in research and will check the eligibility criteria. Finally, when possible, the team will collect their oral consent. Parents will be asked to place the documents (consent form and sociodemographic questionnaire) in an envelope and seal it before returning it to the main teacher for reasons of data confidentiality. Documents will then be collected by the investigation team.

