##### June: Data Collection in Randomly Selected Classes

At the end of school year (June), an investigator will collect data from health records at a specific time during class. In particular, the researcher will look for the presence of de novo HPV vaccination performed by general practitioners outside of the health bus. Signed consent of parents or holders of parental authority will be collected before any intervention in the study (ie, before data collection and before school vaccination is carried out).

Vaccination data, even if not collected at the time of the intervention, can be collected either during the vaccination campaigns, or during the intervention at the end of school year, especially for children whose parents have agreed to participate but not to be vaccinated in the health bus. Indeed, since vaccination dates appear in the health record, it will be possible afterward to know whether pupils were vaccinated before the interventions under study in order to have the vaccination rate at the very beginning of the study.

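### The intervention-only exclusion for prior HPV vaccination has no reference date and is checked after parents receive the program's information, so it can remove girls who started because of the program

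*Protocol article*

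**What the plan says.** The Eligibility Criteria section opens its list with "Exclusion criteria (intervention group only) are as follows". One item is having "already initiated HPV vaccination (complete or incomplete schedule", with no reference date. The sentence then runs on, joined by 'or', to "eligible to participate for collection of data but not for vaccination in the health bus", and sends students with an incomplete schedule to their general practitioner for the missing doses.

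The Objectives section makes information to students and parents the first component of the program, and its first hypothesis is that this information increases uptake. The information reaches parents by one of two routes:

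- **Original route** (Intervention Group section): parent meetings "scheduled at the beginning of school year to inform parents about HPV vaccination and explain this study to them", with consent forms collected at the same meetings.
- **COVID-19 route:** the meetings are replaced by six listed steps. The first is "August-September: Program Information Sent Home to Parents via Students", whose content includes "Written information adapted to student age about HPV vaccination". In October-November the team "will call each authority holder individually by telephone to inform them about HPV vaccination" and checks eligibility in the same call. In November-December an investigator reads vaccination data from the health records.

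The June data collection section adds that vaccination data may also be collected later, that recorded dose dates allow status before the interventions to be worked out afterward, and that new vaccinations by general practitioners will be looked for.

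**The concern.** Information to parents is part of the treatment under test. A criterion that is assessed after this information has gone out, and that carries no date, can be met because of the treatment. Suppose parents read the mailing, take their daughter to the general practitioner in October, and she has one dose on record when eligibility is checked. She is a success of the program, and she also fits the exclusion as written.

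If she is then left out, the intervention group loses the effect that the hypotheses on parent information and on general practitioners predict. She is also an influential girl to lose. The article's two-dose schedule for ages 9 to 14 puts the second dose at least 5 months after the first. A first dose in October therefore leaves time to complete by June, whereas one in February does not. The control school has no such exclusion, so nothing there offsets the loss.

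**Working it through.** **1. Order of events in the intervention school (COVID-19 route, the one with dated steps)**

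| Step | Timing | Section |
|---|---|---|
| HPV information sent to parents | August-September | Program information sent home |
| Telephone information and eligibility check | October-November | Contact with parents |
| Vaccination data read from health record | November-December, or later | Data collection and student sessions; June data collection |
| First bus campaign | December | HPV vaccination in the health bus |

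A first dose given between the first and second rows (or the third, if the record decides) comes after exposure to the program and before the check. On the meeting route, the article's text places HPV information and consent at the same meetings and describes no reading of records before them. The figure with that timeline was not available to me.

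**2. Two readings of the exclusion sentence**

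- *Exclusion from the study.* The item stands in a list headed as exclusion criteria, and the data-collection clause is joined to it by 'or' as if it were one more item. Strengths and Limitations says that exclusion criteria differing between arms may cause selection bias, which would hardly arise if the criteria only governed use of the bus.
- *Exclusion from bus vaccination only.* The data-collection clause can be read as qualifying the items before it, most of which are reasons not to vaccinate. The girl then stays in the denominator.

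The readings give different analysis sets, and the text does not choose between them.

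**3. The plan's own figure**

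Inputs (Sample Size section): 6% control, 20% intervention, α = 0.05, power 0.80. Two-sided testing comes from the statistical methods. With unpooled variance:

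n = (1.960 + 0.842)² × (0.06 × 0.94 + 0.20 × 0.80) / 0.14² = 7.849 × 0.2164 / 0.0196 = 86.7, so 87 per group.

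87 / (1 − 0.15) = 102.4, so 103 per group. Both stated figures reproduce.

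**4. Illustration under the exclusion reading**

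Let e be the share of intervention girls who start because of the program before the check, would complete by June, and are excluded. The documents give no value for e; 1% to 5% is an assumption. The observed proportion is (0.20 − e)/(1 − e). Power is for the two-sided pooled test of 6% against that proportion, with 87 control girls and 87(1 − e) intervention girls, ignoring clustering.

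| e | Observed completion | Power |
|---|---|---|
| 0 | 20.0% | 0.79 |
| 1% | 0.19/0.99 = 19.2% | 0.75 |
| 2% | 0.18/0.98 = 18.4% | 0.70 |
| 3% | 0.17/0.97 = 17.5% | 0.65 |
| 5% | 0.15/0.95 = 15.8% | 0.54 |

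The first row is 0.79 and not 0.80 because the pooled test is slightly less favorable than the unpooled formula. Of 87 girls, 1% to 5% is about 1 to 4 (0.9 to 4.4), against 87 × 0.20 = 17.4 expected completers. With more girls analyzed, power would be higher, but the shift in the observed proportion would be the same.

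**The case against.** The strongest reply is that the exclusion concerns the bus and not the data. The sentence itself mentions data collection, only the intervention school has a bus, and the other listed items are contraindications or similar. The analysis also plainly expects vaccination outside the bus. June data collection looks for it, and the secondary analyses compute, among those who initiated and those who completed, the share who used the bus. Comparisons are by intention to treat, and dose dates are on record. This shows that exclusion from the primary analysis is not certain. It does not settle the scope, because the sentence is still framed as an exclusion and the limitations section treats it as one. The dates are offered for reconstructing the starting vaccination rate and are not tied to the criterion.

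Two stronger readings are tempting and should not be drawn:

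- A reader might infer that the June section places the start of the program too late, because it speaks of consent "before any intervention in the study (ie, before data collection and before school vaccination is carried out". That parenthesis concerns when consent must be signed. The separate sentence on dose dates refers to the interventions under study, and the Intervention Group section counts the mailing among these.
- A reader might infer a large effect. Many early starts at the general practitioner are hard to reconcile with 8.1% coverage at age 16, an assumed 6% control completion, and an expected strong parental veto, with free vaccination in the bus still to come. Nothing in the documents supports a particular share.

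It is also fair to say that the dated sequence belongs to the COVID-19 route, and that any loss works against the intervention and cannot create a false positive.

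**Conclusion.** The point holds in a limited form. Parents receive part of the program before vaccination status is read and, on the COVID-19 route, before eligibility is checked. The intervention-only exclusion has no reference date. Read literally, and in line with the article's own remark on selection bias, it can remove girls whose vaccination the program caused. Whether it does so in the primary analysis depends on a sentence that admits two readings.

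The direction is known if girls are lost: the intervention proportion falls, with underestimation and loss of power as the result. The size is not known. The figures of 19.2% to 15.8% instead of 20%, and of 0.75 to 0.54 instead of 0.79 for power, rest on an assumed 1% to 5% of girls, all of them excluded and all of them would-be completers. The article already concedes that the sample is probably too small because clustering was ignored, so there is little margin for an avoidable loss. This goes beyond detail left to an analysis plan, because the rule as stated would itself produce a post-exposure exclusion.

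**What to change.** 1. For the analysis, define prior initiation as a first dose dated before the first program information to parents (the meeting or the mailing, whichever route was used). Derive it from the dated health records, with the same calendar cut-off in both schools.
2. Keep every girl whose first dose is dated on or after the cut-off in the primary and initiation analyses, wherever the dose was given.
3. Reconcile the Eligibility Criteria sentence so that it says whether the criterion affects study entry, the analysis set, or only use of the bus.

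The consent sentence in the June section needs no change. Who may be vaccinated in the bus is a care question that this point does not address.

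The cost is one definition and one derivation rule. Dose dates already stand in the health records that the team reads in both schools, so no new variable is needed. Recruitment for vaccination is complete and the article describes analyses as ongoing, so the rule should be fixed before the primary comparison is final. The report should give the number of girls already set aside under the criterion and, where their records were collected, whether the first dose fell before or after the cut-off.
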